## Abstract

**Background:**

Obesity, overweight and unemployment are interlinked, with debilitating effects on mortality, health, wellbeing and quality of life. Existing interventions to reduce overweight, obesity and unemployment have addressed these challenges independent of each other with limited success. The Adding to Social capital and individual Potential In disadvantaged REgions (ASPIRE) project will develop an innovative model using a combination of skills training and health and wellbeing interventions to improve health, wellbeing, quality of life and reduce overweight, obesity and unemployment in England and France. The aim of this paper is to outline the protocol for evaluating the ASPIRE project to examine the effectiveness of the intervention and clarify the mechanisms and contextual factors which interact to achieve outcomes.

**Methods:**

A mixed-method realist evaluation using a single-group before-and-after design will be used. The evaluation will consist of development of an initial programme theory, theory validation and refinement using quantitative and qualitative data to understand the causal mechanisms, contexts of implementation and their interactions that result in outcomes observed in ASPIRE. Primary outcomes that will be assessed are change in body weight and body mass index, reemployment and a rise on the ASPIRE participation ladder. The ASPIRE participation ladders consists of a series of 5 steps to engage participants in the project. The first step on the ladder is joining an ASPIRE hub with paid employment as the final step on the ladder. Secondary outcomes will be physical activity, diet quality, self-efficacy and health-related quality of life. Both quantitative and qualitative approaches are appropriate in this study because the use of validated questionnaires and objective measures will demonstrate how much the intervention addressed outcomes related to weight loss and reemployment and the qualitative data (photovoice) will provide insights into the contexts and experiences that are unique to participants in the project.

**Discussion:**

The results from this evaluation will provide an understanding of how a model of health-related interventions which improve health, wellbeing and maintenance of a healthy lifestyle could reduce overweight, obesity and unemployment. The findings will enable the adaptation of this model for effective implementation in different contexts and circumstances.

**Trial registration:**

ISRCTN registry: Study ID: ISRCTN17609001, 24th February 2021 (Retrospectively registered).

**Supplementary Information:**

The online version contains supplementary material available at 10.1186/s12889-021-10523-3.

## Background

Obesity is a leading risk factor for the global burden of diseases [1] and a major contributor to all-cause mortality, morbidity and decline in both quality of life and life expectancy [2–4]. Of a greater concern is recent data showing that individuals with obesity are at a greater risk of morbidity and mortality from the coronavirus disease 2019 (COVID-19) [5–7]. Data from the Health Survey for England (HSE) indicates an overweight and obese prevalence of 66.9% in adult men and 59.7% in adult women [8]. In France, the prevalence of overweight (including obesity) in adults was 54% in men and 44% in women [9]. Apart from being a health risk factor, obesity is strongly associated with unemployment, social disadvantages and reduced socioeconomic productivity [10] and poor individuals in Europe are 10–20% more likely to be obese compared to individuals in high income brackets [11–13].

Consistent with global trends, obesity across the France Channel English (FCE) area (south and east coasts of England and the north coast of France) is a significant concern. In this region, high levels of obesity have been shown to coincide with high rates of unemployment. In the British household Panel Survey (BHPS), job loss was associated with weight gain of 1.56 kg/year and with significant decline in wellbeing and increased sleep deprivation [14]. Several causal pathways have been postulated to explain the link between unemployment or socioeconomic deprivation and high body mass index (BMI). Unemployment leads to more households experiencing a decrease in income, which calls for new strategies to cope with restrained household budgets and may lead to unhealthy diets. Individuals in lower income households are increasingly consuming diets which are able to satisfy caloric needs but are poor in micronutrient density, dietary variety and high in sugar and fat, leading to poorer health outcomes [15]. Data from the HSE survey shows that only 29% of adults consumed the recommended five portions of fruit and vegetables a day. Higher consumption of fruit and vegetables was also associated with higher income, and vice versa: 36% of all adults in the highest income quintile had consumed five or more portions of fruit and vegetables on the previous day compared with 23% of all adults in the lowest quintile [16]. Fresh, local, healthy food options are often more expensive and are more difficult to cook, therefore individuals cope by buying much cheaper food (highly processed meat products, high fat and sugar foods) or resort to ‘take-aways’ or ‘fast food’ which require no cooking [13, 17, 18].

Additionally, of those in the highest income quintile, 42% of men and 34% of women undertake at least five 30-min sessions of moderate or intensive physical activity (PA) per week, compared to 31 and 26%, respectively, in the lowest quintile [19]. Data from the French Health Study on Environment, Biomonitoring, Physical Activity and Nutrition (Esteban) showed that 53% of women and 71% of men achieved the World Health Organisation (WHO) recommendations on physical activity for health however, 90% of adults reported more than 3 h of sedentary activities per day and 42% of adults more than 7 h [20]. More recent data also showed that during the coronavirus pandemic, half of the population did not meet the recommendations for physical activity and one third reported a high level of sedentary lifestyle [20]. Insufficient physical activity was also more prevalent in people in lower professional categories, with no professional activity, women with fewer qualifications, time off work or partially unemployed [20].

In contrast obesity is considered a cause for lower income when obese people drift into lower-income jobs due to labour–market discrimination and public stigmatisation [21]. Research suggests that obese individuals are more likely to be perceived as lazy, unsuccessful, weak-willed and undisciplined resulting in negative discrimination due to body weight in the labour market, including higher job insecurity and lower chances of obtaining a job [22, 23]. In a longitudinal study using data from over 120,0000 adults across 21 European countries, obesity decreased employment chances and chronic conditions linked with high BMI negatively affecting employment likelihood and increased the intention to retire early [24]. Furthermore, psychological distress and subsequent emotional eating as a consequence of both obesity and unemployment provide a serial pathway linking unemployment to obesity. Maladaptive coping strategies, such as eating energy-dense foods to alleviate negative emotions and stress, coupled with stress-induced disturbances to metabolic signals promote weight gain and obesity over time [25]. The negative social, psychological, emotional, and behavioural consequences of obesity exacerbate psychological distress and maladaptive eating behaviours, can thus create a cyclic mechanism [25].

Although it has been well established that obesity and unemployment are strongly linked, existing services to tackle obesity and unemployment rarely work together to address the issue holistically. Additionally, there is a lack of interventions examining how the underlying causes of unemployment and obesity can be addressed using common strategies. The main public health interventions used to tackle obesity focus on information campaigns, advertising, labelling rules and regulation of nutritional claims [26]. While these types of interventions inform people about food characteristics, they are not able to successfully induce people to make healthier food choices. Interventions focused on improving the income of economically disadvantaged individuals with the additional effect of improving health are required. Further research is also needed on how individuals with obesity can best be supported to obtain and maintain employment.

The Adding to Social capital and individual Potential In disadvantaged REgions (ASPIRE) is an innovative project which seeks to create a new model for service delivery combining healthy weight and employability services to address unemployment and obesity in the FCE region. The ASPIRE project will target the obese, overweight and unemployed population across the FCE zone, using food production as a way to increase awareness and engagement, reduce weight, increase self-esteem, improve employability via new skills and work experience. ASPIRE will improve the quality and effectiveness of service delivery to socio-economically disadvantaged communities by co-ordinating healthy lifestyle opportunities with a pathway into employment. The health-based interventions co-created with ASPIRE partners will be adapted to socially and economically disadvantaged communities to reduce obesity and overweight and increase employability.

This paper is a protocol outlining the evaluation of the ASPIRE model. The aim will be to evaluate the ASPIRE model using Realist Evaluation (RE) methods to examine which ASPIRE interventions work, for whom, why and under what contexts.

## Methods

This evaluation is designed as a multidisciplinary and mixed-method process and will use RE methods to examine the effectiveness of the ASPIRE model. Realist evaluation uses key linked concepts (‘mechanism’, ‘context; and ‘outcomes’) for explaining and understanding programmes. This is known as the CMO configuration [27]. A CMO configuration is a proposition stating what it is about an intervention that works, for whom and in what circumstances. This approach will enable the development, validation and refinement of mid-range theories that account for how the *Context* in which ASPIRE intervention activities are implemented influence intervention *Mechanisms* (e.g. participants reasoning in uptake of interventions) to produce intended and unintended *Outcomes* (decrease in weight, BMI or unemployment). Realist evaluations assume that the success or failure of interventions are dependent on certain conditions, complex interactions of causal mechanisms and are heavily influenced by the way that different stakeholders respond to them [27]. Context refers to broad social or geographical features as well as factors affecting the implementation of programs (e.g. setting of intervention, adequate funding, the qualifications of staff) [27–29]. The context within which a project is implemented can influence the way in which, or the extent to which, a programme is implemented, who it targets and who it reaches. The mechanism is the underlying causal process which informs how and why an intervention works and for which participants [27]. Mechanisms can be intended and unintended, generating both positive and negative outcomes and are filtered through people, who have an ability to interpret and respond to them differently [27, 28, 30]. Therefore, evaluation of an intervention’s effectiveness should include how different people experience and respond to it and why. The RE method is particularly suited to evaluating new and complex interventions that seem to work but ‘for whom and how’ is not yet understood. While several of the interventions incorporated in the ASPIRE model have been used to independently reduce overweight or obesity and unemployment, there is limited evidence on how the combination of such interventions work holistically to reduce obesity and unemployment. The conceptual framework using CMO configuration to map the pathway from intervention to outcomes is illustrated in Fig. 1. This framework will be continuously validated and refined during data collection and analysis. The conduct and reporting of the evaluation will be guided by the Realist and Meta-Review Evidence Synthesis Evolving Standards (RAMESES II) reporting standards for realist evaluations [31].

**Fig. 1 Fig1:**
[figure not shown]
Conceptual framework illustrating the contexts-mechanism-outcome configuration underlying the ASPIRE model. **Abbreviations:** BMI, body mass index, CV, curriculum vitae, PA, physical activity

### Initial Programme theory

The initial programme theory represents the underlying assumptions about how interventions implemented in ASPIRE are meant to work and what impacts they are expected to have. The development of the initial programme theory will consist of a critical realist synthesis of international literature to identify interventions used to reduce overweight, obesity and unemployment. Additionally, information on common approaches used in these interventions, the contexts and mechanisms that have contributed to the success or failure of the interventions will also be extracted to help refine the final programme theory. Gap and strengths, weaknesses, opportunities, threats (SWOT) analyses will also be conducted in collaboration with stakeholders to help identify existing resources within organisations which could enhance the implementation of the ASPIRE model. Furthermore, weaknesses and threats to the project will be identified and strategies will be implemented to mitigate the risks identified. An evaluation toolkit comprising of qualitative and quantitative data collection methods and tools have been identified and co-created with partners to be used with ASPIRE participants and providers to evaluate the efficacy of the ASPIRE project over its life course. The completed detailed programme theories developed will help to explore the relations between context, processes or mechanisms and outcomes (CMO configurations) to aid the refinement of the final programme theory.

### Final Programme theory

Theory refinement and validation will include adaptation and pilot testing of the qualitative and quantitative data collection tools, followed by subsequent data collection on outcomes to validate and refine programme theories. Different qualitative and quantitative methods will be used to understand and validate programme theories that link context, mechanisms and outcomes of the ASPIRE model. Subgroup analyses grouped by responders vs. non-responders, sex, site location (urban vs. rural), duration of unemployment (long-term vs. short-term) will be conducted to further clarify which sub-groups were reached by the programme, whether outcomes varied across sub-groups and why. This process will elucidate the contexts and mechanisms under which ASPIRE is effective and help to understand how and why the ASPIRE model works in different contexts. This will enable stakeholders and implementers including local and national authorities, employment services, small and medium-scale enterprises (SMEs) and health service providers make decisions about which interventions to embed in existing services, and how to adapt them to different circumstances.

### Study design

#### Setting

The ASPIRE project will be implemented across the 7 sites located in the FCE region. The FCE area covers the south and east coasts of England from Cornwall to Norfolk, and the north coast of France from Finistère to Pas-de-Calais. The sites in France are located in Peronne (FR223 Somme), Abbeville (FR223 Somme), Wimereux (FR302 Pas-de-Calais) and Loos-en-Gohelle (FR302 Pas-de-Calais). The sites in the United Kingdom are located in Aylesham (UKJ44 East Kent), Medway (UKJ41 Medway), and Boscombe (UKK21Bournemouth and Poole). The implementation partners are already involved in services providing healthy lifestyle, wellbeing and employability activities and have extensive experience in working with hard-to-reach, vulnerable and socially isolated individuals and communities.

#### Participants

Participants for the study will be recruited from communities within the 7 ASPIRE implementation sites. Recruitment will be carried out at community and unemployment centres, via flyers, online posts, posters and referrals from general practitioners, weight management clinics and social prescribing. Participants are eligible if they meet the inclusion criteria. Inclusion criteria will be adults (18 years above) who are unemployed, jobseekers or living with overweight or obesity (BMI between 24 kg/m^2^ and 40 kg/m^2^) using WHO classification [32] and ability to participate in activities. A lower BMI cut-off of 24 kg/m^2^ was chosen to include individuals at risk of becoming overweight and to capture participants with the risk of developing other chronic diseases. Exclusion criteria will be as follows: terminal illness or palliative care, dementia, a severe mental health problem or learning difficulty; serious health conditions that will affect uptake of intervention activities; planned bariatric or weight loss surgery; serious psychosocial problems or behavioural problems that could hinder participation in interventions (e.g. drug addiction, serious psychiatric disorders, aggressive delinquent behaviour); pregnant or planning to become pregnant and individuals currently involved in full-time paid employment or recurrent short-term contracts. Individuals who do not meet the eligibility criteria because of serious health conditions will be referred to local general practitioners or the appropriate health service provider. Ethical approval has been obtained in line with the Bournemouth University Research Ethics Committee Code of Practice (Ethics ID: 33136). Informed consent will be obtained from participants prior to enrolment in the intervention. Participants who respond to the study invitation will receive a participant information sheet with detailed information concerning the project, the nature and objectives of the study and possible risks associated with their participation and will be required to sign a consent form before participating in activities at the ASPIRE hub. All data collected for this project will be anonymised and no identifying characteristics of respondents will appear in final manuscripts, reports and publications.

#### Sample size

Power calculations to determine sample size were carried out using G Power 3.1.9.4 software (version 3) statistical power calculator. This indicated that a minimum sample size of 871 was needed to detect a weight loss difference of 1.9 kg between baseline and follow-up with a power of 90%, at α = 0.05 and effect size of 0.11. These estimations were derived from a previous study investigating the effect of cognitive behaviour therapy lifestyle intervention on weight and other health outcomes [33]. An additional sample of 15% was added to account for unpredictable effect on statistical power of clustering cases by site. To allow for attrition and ensure sufficient power during the follow up period, an attrition rate of 30% was estimated between enrolment and follow up assessment, bringing the total sample size to 1303 participants.

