### Data collection

Consistent with realist principles and methodology, a mixed-method approach will be used for data collection. This will involve collecting both quantitative and qualitative data to refine the final programme theory on what aspects of the interventions in ASPIRE work, for which participants and in what context. The quantitative assessments will be used to objectively measure the outcomes which occur as a result of the intervention and qualitative assessments will provide more insights into why the interventions were effective or failed to achieve the desired outcome. Using a one-group pre-post methodology, participants will be followed up over time and data will be collected at four time points T0 (at the beginning of ASPIRE), T1 (at 12 weeks), T2 (at 6 months) and T3 (at 9 months) to map participants’ journey through the programme. At baseline (T0), the intervention will be explained to the potential participant and the consent will be obtained from the participant. This will be followed by administration of baseline questionnaires and measurement of baseline anthropometrics. All questionnaires used for data collection will be available in both French and English to ensure that no participants are excluded on the basis of language. Evaluation materials will be piloted to ensure consistency, comprehension, clarity of questions and coherence of both English and French versions and appropriate modifications will be made. A standard operating procedure for data collection has been developed and training on the evaluation and data collection process will be provided to project coordinators at the ASPIRE hubs to ensure accuracy and adherence to international standards for assessing anthropometry.

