### Data analysis

Statistical analysis of quantitative data will be conducted using Statistical Package for Social Sciences (SPSS) IBM statistics (version 26, SPSS UK Ltd. Chertsey, UK). The normality of continuous variables will be checked using QQ-plots and the Shapiro-Wilk test. All tests will be carried out at the 95% confidence interval and in all analyses, a threshold of *p* < 0.05 will be considered statistically significant. Chi-square tests for independence will be used for comparing categorical variables such as sex and employment status. Means and standard deviations will be computed for continuous variables including age, body weight and BMI. Paired t-tests and repeated measures analysis will be used to examine the effect of the intervention on body weight and BMI of participants over time. Correlations and regressions or non-parametric equivalents as appropriate will be used to examine the relationships between continuous variables. The contribution of demographic variables to predicting BMI and behaviour change will be assessed using multiple linear regressions. The analysis will be conducted using intention-to-treat principles and for completers only.

Qualitative data (photos and transcript form semi-quantitative interview) will be analysed using NVivo Pro 12.5 (QSR International, 2020), which permits the coding of photos as well as text. Interviews will be audio recorded with the participants’ consent and transcribed. Thematic analysis and content analyses using both deductive and inductive approaches [48] will be used to test initial theories while allowing for emergence of new themes, and will include stages of familiarisation, coding, indexing and charting, mapping and interpretation. The deductive analysis will enable to test whether data are consistent with prior assumptions and theories identified during the development of the initial programme theory. The inductive approach which is guided by specific evaluation objectives will allow research findings to emerge from the frequent, dominant, or significant themes inherent in the raw data.

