Strengths of this protocol include the use of a multidisciplinary and mixed-method realist evaluation approach to provide a better understanding of the complexity of interventions to reduce overweight, obesity and unemployment. Because of the complex and multifactorial causal factors underlying obesity and unemployment, interventions seeking to address these are equally complicated and require a comprehensive understanding of intervention context, implementation, mechanisms and outcomes which can be achieved using a realist evaluation approach. The pre-post evaluation method chosen will also minimise the effect of interindividual variation on outcomes.

In conclusion, the novel findings from this evaluation will contribute to international, European, national and regional strategies and policies to address the current challenges of obesity, overweight and unemployment. Additionally, experiences from the implementation of ASPIRE will be embedded in existing services to enhance the quality and effectiveness of interventions that individuals who are overweight, obese or unemployed can receive. Furthermore, participants and their families will benefit immensely through the maintenance of a healthy lifestyle and the model can be adapted by any community looking to make healthy lifestyle changes.

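### The stated 1.9 kg, effect size 0.11 and 871 participants imply a 17.3 kg SD of within-person weight change, so 871 is not the number needed for 1.9 kg

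*Protocol article*

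**What the plan says.** Under Sample size, the protocol article states that "a minimum sample size of 871 was needed to detect a weight loss difference of 1.9 kg between baseline and follow-up". The other inputs it names for this calculation are 90% power, a significance level of 0.05 and an "effect size of 0.11". It gives the source only in general terms: "These estimations were derived from a previous study investigating the effect of cognitive behaviour therapy lifestyle intervention on weight and other health outcomes". It states no SD of weight, no SD of weight change and no baseline/follow-up correlation. The 871 is then inflated by 15% ("An additional sample of 15% was added to account for unpredictable effect on statistical power of clustering cases by site") and by 30% for attrition, to reach 1303.

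The comparison is within person. Data collection says "Using a one-group pre-post methodology, participants will be followed up over time", and Data analysis says "Paired t-tests and repeated measures analysis will be used to examine the effect of the intervention on body weight and BMI". The Discussion counts this as a strength: "The pre-post evaluation method chosen will also minimise the effect of interindividual variation on outcomes".

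**The concern.** In a paired design, the SD that governs power is the SD of each person's change, not the spread of weight between people. The article gives both a difference in kilograms and a standardised effect size for the same comparison, so the SD behind them can be read off. It has the size of a between-person SD of body weight. The sample size then does not reflect the gain from pairing that the Discussion claims.

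At stake is the stated basis for enrolling 1303 people at seven sites, since both inflations are applied to 871. If the SD of change is smaller than the figures imply, the sample has more than 90% power for 1.9 kg and will detect smaller changes than the one named. A reader of the results should be able to see that from the protocol.

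**Working it through.** **Inputs from the article.** Difference 1.9 kg, effect size 0.11, power 90%, α = 0.05 (sidedness not stated) and n = 871 come from Sample size. The one-group pre-post design and the paired t-test come from Data collection and Data analysis.

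**Step 1: reproduce 871.** For a paired t-test, dz = mean change / SD of change.
- Normal approximation, two-sided: n = ((1.960 + 1.282)/0.11)² ≈ 869.
- Noncentral t, two-sided: power is 0.8999 at n = 870 and 0.9002 at n = 871, so n = 871 exactly.
- One-sided α = 0.05 would give 710. Two independent groups with effect size 0.11 would give 1737 per group.

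So 871 is the two-sided paired calculation with dz = 0.11, and its arithmetic is right.

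**Step 2: the SD this requires.**
- SD of change = 1.9/0.11 = 17.3 kg.
- Rounding of 0.11 (0.105 to 0.115) gives 1.9/0.115 = 16.5 kg to 1.9/0.105 = 18.1 kg.
- If changes were normal around a mean loss of 1.9 kg, 95% would lie within ±1.96 × 17.3 = ±33.9 kg of it, that is, from a loss of about 36 kg to a gain of about 32 kg.

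That spread is not credible for a lifestyle programme with assessments to 9 months that excludes people planning weight-loss surgery.

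**Step 3: what 17.3 kg might be.** If it is the between-person SD of weight, and is the same at both visits, then SD of change = 17.3 × √(2(1 − r)), where r is the baseline/follow-up correlation. The values of r are assumptions.

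| r | SD of change (kg) | n for 1.9 kg, 90% power |
|---|---|---|
| 0.50 | 17.3 | 874 |
| 0.80 | 10.9 | 351 |
| 0.90 | 7.7 | 177 |
| 0.95 | 5.5 | 90 |

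The n at r = 0.50 is 874 rather than 871 only because 17.27 was rounded to 17.3. The two SDs coincide only at r = 0.5, which is low for repeated weighing of the same adults.

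**Step 4: the consequence over a range of SDs of change.** The SDs are assumptions, as the article gives none. The n is the paired t-test, two-sided 0.05, 90% power. The detectable difference with 871 pairs is 3.2415 × SD/√871 = 0.1098 × SD.

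| SD of change (kg) | n for 1.9 kg | 871/n | Detectable with 871 independent pairs (kg) |
|---|---|---|---|
| 5 | 75 | 11.6 | 0.55 |
| 6 | 107 | 8.1 | 0.66 |
| 8 | 189 | 4.6 | 0.88 |
| 10 | 293 | 3.0 | 1.1 |
| 12 | 422 | 2.1 | 1.3 |
| 15 | 657 | 1.3 | 1.6 |

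The last column treats pairs as independent. Clustering by site would raise those values.

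**The case against.** The strongest reply is that nothing has been miscalculated: 871 is correct for the stated effect size, α and power, and the text calls it a minimum. The doubtful element is an input taken from a study that the reader of the article cannot inspect. The error is also in the safe direction for weight, and a sample of this size may be wanted for re-employment or for the subgroup analyses listed under Final Programme theory. All of this stands, but none of it rescues the sentence. Three figures are stated for one paired comparison, and together they need an SD that such a comparison would not plausibly have.

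Four stronger readings are tempting, and the article does not support them.
- A reader might infer that 871 is wrong by a known multiple. The multiple depends on an SD of change that is not given, and runs from 1.3 to 11.6 over the range shown.
- A reader might infer that the baseline/follow-up correlation was left out. An omitted correlation, an assumed correlation of 0.5, or 0.11 and 1.9 kg being different quantities in the cited study would all give the same text.
- A reader might infer that trivial losses will be declared significant. For example, with an assumed SD of 6 kg and 912 completers (1303 × 0.70), 1.96 × 6/√912 = 0.39 kg reaches p < 0.05. That treats completers at seven sites as independent, and the plan itself allows for clustering. Its own 15% alone gives 0.39 × √1.15 ≈ 0.42 kg, and stronger clustering would raise it further.
- A reader might want a rule that significance below a named loss does not count as success. That is a matter of interpretation, separate from this error, and may be settled in an analysis plan that is not shown.

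**Conclusion.** The point holds as an inconsistency between stated figures. That 871 is the paired answer for 0.11, and that 0.11 with 1.9 kg requires an SD of change of 17.3 kg (16.5 to 18.1 kg), follows from the article alone. That such an SD is implausible for within-person change is a judgement, but a safe one given the range of individual changes it implies. The claim that 871 are needed for 1.9 kg at 90% power is therefore wrong as written, in the direction of oversizing. The trial is not underpowered for weight on this account, and no planned analysis is invalidated.

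The size of the excess rests on an assumed SD of change: about 3-fold or more up to 10 kg, about 2-fold at 12 kg and 1.3-fold at 15 kg.

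**What to change.** Rewrite the Sample size paragraph in three respects.
1. State the SD of weight change, or the SD of weight together with the baseline/follow-up correlation, from the cited study or from pilot data.
2. Reconcile 0.11, 1.9 kg and 871 using that SD, and say that the calculation is a two-sided paired t-test.
3. Restate either the difference that the planned sample can detect at 90% power or its power for 1.9 kg, with the allowance for clustering by site made explicit.

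If 1303 is kept, say which other objective it serves, such as re-employment or the planned subgroup comparisons. The cost is one paragraph and a look at the cited study's data. Recruitment need not change.

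### The 30% attrition allowance was applied as n × 1.30 instead of n ÷ 0.70, so enrolling 1303 does not leave the 1002 completers the plan requires

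*Protocol article*

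**What the plan says.** The Sample size section of the protocol article builds the total in three steps.

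1. G*Power supplies the starting figure of 871. The target is a mean weight change of 1.9 kg from baseline, and the calculation was run "with a power of 90%, at α = 0.05 and effect size of 0.11".
2. The clustering step follows: "An additional sample of 15% was added to account for unpredictable effect on statistical power of clustering cases by site".
3. The last step covers loss of participants: "an attrition rate of 30% was estimated between enrolment and follow up assessment, bringing the total sample size to 1303 participants".

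The section does not name the test, its sidedness or the formula for the attrition step. The Data analysis section names the analysis of the weight outcome: "Paired t-tests and repeated measures analysis will be used to examine the effect of the intervention on body weight and BMI". Nothing else in the article alters the total of 1303.

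**The concern.** The 30% is described as a loss between enrolment and follow-up, so it is a fraction of those enrolled. If 30% of enrolled participants are lost, 70% remain, and the required number of completers must be divided by 0.70. Adding 30% to the required number is a different operation and covers a smaller loss. The printed total looks like the result of the addition.

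The total is offered as sufficient to keep power once attrition has occurred. If the attrition step is wrong, the study cannot have the 90% power, the 15% clustering allowance and the 30% attrition allowance together at 1303.

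**Working it through.** **Inputs, from the Sample size section unless noted**

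- Effect size 0.11, α = 0.05, power 90%, minimum n = 871
- Clustering allowance +15%
- Attrition 30%, enrolment to follow-up
- Stated total 1303
- Paired t-test (Data analysis section). The two-sided form is inferred because it reproduces 871.

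**Step 1: the minimum.** Paired t-test, noncentral t distribution with noncentrality 0.11 × √n and n − 1 degrees of freedom, two-sided α = 0.05:

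- n = 870: power 0.8999
- n = 871: power 0.9002

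So 871 is reproduced exactly. A one-sided test would give 710.

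**Step 2: clustering.** 871 × 1.15 = 1001.65, rounded up to 1002. This is the number needed with follow-up data.

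**Step 3: attrition.**

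- Multiplying: 1002 × 1.30 = 1302.6, which rounds to 1303, the stated total. Without the intermediate rounding, 1001.65 × 1.30 = 1302.1, which rounds up to 1303.
- Dividing: 1002 / 0.70 = 1431.4, so 1432 (1431 if 1001.65 is not rounded first).

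Other routes do not give 1303:

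| Route | Result |
|---|---|
| 871 / 0.70 | 1245 |
| 871 × 1.45 | 1263 |
| 871 / 0.85 × 1.30 | 1333 |
| 871 / 0.85 / 0.70 | 1464 |

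**Step 4: what 1303 leaves.**

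- Completers at 30% loss: 1303 × 0.70 = 912
- Shortfall in completers: 1002 − 912 = 90
- Shortfall in enrolment: 1432 − 1303 = 129
- Largest attrition that still leaves 1002: 1 − 1002/1303 = 23.1%

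**Step 5: power with 912 completers.** The effective number is 912 divided by (1 + the cost of clustering). Power is then computed as in step 1, at effect size 0.11:

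| Cost of clustering | Effective n | Power |
|---|---|---|
| 0% | 912 | 91.3% |
| 4.7% | 871 | 90.0% |
| 10% | 829 | 88.6% |
| 15% (the plan's allowance) | 793 | 87.2% |

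The 4.7% row is the break-even point, 912/871 = 1.047.

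**The case against.** The strongest reply is that 912 completers is still more than 871, the only number the article ties to 90% power. With no clustering effect, power at 30% attrition would be 91.3%. The article calls the clustering effect unpredictable and gives no intraclass correlation or design effect, so the 15% can be read as a contingency rather than a known cost. On that reading 87.2% is the unfavourable end of a range from 87.2% to 91.3%, and even there the loss is under 3 percentage points. The 30% is itself only an estimate.

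All of this stands as a limit on the size of the harm, but it does not rescue the total. The plan added the 15% to protect power and then applied attrition to the enlarged figure, so its own requirement after loss is 1002. The attrition slip leaves 4.7% of margin for clustering where the text claims 15%.

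A second reply is that the planned intention-to-treat and repeated measures analyses may keep some participants who miss a visit. The article gives no missing-data method to support this. It also plans a completers-only analysis and paired t-tests, which need a follow-up weight, and its sample size paragraph itself treats attrition as a threat to power.

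The attrition formula is inferred rather than stated. The inference is strong, because multiplication gives the printed total exactly and none of the alternatives tried does.

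**Conclusion.** The concern holds. The stated total of 1303 provides for 23.1% attrition, not the 30% named beside it. On the plan's own effect size, two-sided α and 15% clustering allowance, 30% attrition leaves 912 completers instead of 1002 and power of 87.2% instead of 90%. Enrolment that meets all the stated assumptions is 1432.

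The 87.2% assumes that clustering uses the whole 15%; power stays at or above 90% if clustering costs no more than 4.7%. The effect is modest and does not threaten the study, but a headline design figure fails its own specification and should be corrected.

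**What to change.** Correct the sample size paragraph so that its numbers agree. No extra enrolment is needed if the claim is restated. Suggested content:

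- Enrolling 1303 gives about 87% power at 30% attrition with the full 15% clustering allowance, or 90% power for attrition up to 23%.
- At 30% attrition about 912 participants remain. This still exceeds the minimum of 871 before the clustering allowance.
- The attrition formula should be written out as the required number of completers divided by (1 − attrition rate).

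If 90% power at 30% attrition with the 15% allowance is to remain the claim, the total to print is 1432, at a cost of 129 further enrolments.

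The restatement costs a sentence or two of text and a stated power about 3 points lower. The planned analyses do not change.
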